### Recruitment

Participants will be recruited via MRFGR. All payment of participants will be handled by the panel agency. Participants are awarded with points which they receive after completing the survey. The number of points depends on the length of study and can be redeemed in cash or vouchers (i.e. Amazon). Respondents can redeem their cash after cumulating 150 points or more (equating to £15).

### Inclusion/exclusion criteria

Smokers will be matched to the target population of smokers as described above. Inclusion criteria are: adult aged 18+, resident in the UK, fluent in English. Exclusion criteria are: under 18 years of age, resident outside of the UK, exclusive vapers, dual users (i.e. concurrent use of e-cigarettes and any tobacco consumption), former smokers, and non-fluent in English. Inclusion and exclusion criteria will be communicated to participants before they provide consent.

### Measures

#### Baseline measures

Demographic variables will include gender, age, ethnicity, occupation and economic activity and highest attained qualification in line with data collected by the Office for National Statistics (ONS). Occupation will be measured with a single item questionnaire using four categories ‘routine and manual’, ‘intermediate’, ‘managerial and professional occupation, ‘never worked & long-term unemployed’ [46].

Smoking status will be classified as ‘never smoked’ (individuals who have smoked fewer than 100 cigarettes in their life time and have not smoked in the past 30 days), ‘daily smoker’ (anyone who has smoked daily for the past 30 days and has smoked more than 100 cigarettes in their life time), ‘non-daily, occasional and social smoker’ (individuals who do not smoke every day but, for example, might smoke once a week providing they have smoked more than 100 cigarettes in their life time and in the past 30 days) based on the criteria European risk monitoring project [35, 47, 48].

For smokers, motivation to quit will be measured using the validated single-item instrument, Motivation to Stop Scale (MTSS), which measures intention, desire to stop smoking and the immediacy of their intended quit date (e.g. “I don’t want to stop smoking, I REALLY want to stop smoking but I don’t know when I will, I REALLY want to stop smoking and intend to in the next 3 months, I REALLY want to stop smoking and intend to in the next month”) [49]. Cigarette dependence will be measured using the Fagerström Test for Cigarette Dependence (FTCD) (e.g. the number of cigarettes smoked per day, time to first cigarette of the day, etc.) [50].

### Stimuli development

#### Comparative health message formulation

A pilot study will be conducted to generate the most appropriate comparative health message from a list of eight messages (which were selected from an initial list of 26 on the basis of receiving the highest ratings previously from seven experts in the field). This will provide a robust comparative health message that has been evaluated for accuracy, persuasiveness and clarity by a panel of experts before being tested in a pilot study of 1000 participants (non-smokers and smokers) on comprehensibility, credibility and convincingness. The chosen health message will be displayed on various e-cigarette packages in line with the current EU-TPD requirements to ensure consistency (i.e. occupy 30% of the surface of the pack, printed in black Helvetica bold type on a white background) as described above.

#### Outcome variables

Prior to, and following the experimental exposure to one of the e-cigarette health messages described above (each presented for a standardised period of 30 s), perceptions of e-cigarettes and intentions will be measured on the following scales: i) harmfulness, ii) addictiveness and ii) socially acceptable, iv) effectiveness as a cessation aid, v) intention to use, vi) intention to purchase and, for smokers only, vii) intentions to quit and use e-cigarettes in a future quit attempt (all on a 7-point rating scales with the anchors “Extremely, to Not at all” scored from 7 to 1; see Table 1 for the full list of constructs). In order to minimise response bias, unrelated (filler) questions will be presented following exposure of the message stimuli in addition to the aforementioned outcome measures. Examples of such questions will include the following: “Which e-cigarette did you find the most appealing?”; “Which e-cigarette (if any) would you be most likely to use?”; “Which e-cigarette did you think looked most like a cigarette?”. Participants will also be asked: “Did you notice a health message on the e-cigarette pack?”; “Did you think the health message was positive, negative, neutral?”

**Table 1 Tab1:** List of constructs (outcome measures)

Constructs	Statements	Anchors
Perceptions of e-cigarettes	How harmful do you think e-cigarettes are?	☐ Extremely (…) ☐ Not at all
	How addictive do you think e-cigarettes are?	☐ Extremely (…) ☐ Not at all
	How socially acceptable do you think e-cigarettes are?	☐ Extremely (…) ☐ Not at all
	How effective do you believe e-cigarettes to be as a quit aid	☐ Extremely (…) ☐ Not at all
Intentions	How likely are you to use an e-cigarette	
	a) in the next month b) in the next 6 months	☐ Extremely (…) ☐ Not at all ☐ Extremely (…) ☐ Not at all
	How likely are you to purchase an e-cigarette	
	a) in the next month b) in the next 6 months	☐ Extremely (…) ☐ Not at all ☐ Extremely (…) ☐ Not at all
	For smokers only	
	How likely is it that you will make a quit attempt:	
	a) in the next month b) in the next 6 months	☐ Extremely (…) ☐ Not at all ☐ Extremely (…) ☐ Not at all
	How likely are you to use an e-cigarette in a quit attempt	
	a) in the next month b) in the next 6 months	☐ Extremely (…) ☐ Not at all ☐ Extremely (…) ☐ Not at all

Note: Each of these statements will be presented prior to and following exposure to one of the e-cigarette health messages

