**Discussion:**

Health warnings, such as those implemented by the TPD, may help to prevent non-smokers from e-cigarettes use, but it is possible that they may inadvertently deter smokers from initiating use and substituting their tobacco smoking for e-cigarettes use if their content is deemed too negative. It is hoped that this study will help identify the most effective message or combination of messages that encourage use among smokers without promoting use among non-smokers.

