## Background

Health warnings on cigarette packets can be an effective tool to increase awareness about the dangers of smoking. Research suggests that they can act as a deterrent to smoking and promote cessation [1, 2]. Consequently, as part of a comprehensive tobacco control strategy, tobacco warning labels have become central to anti-smoking education campaigns worldwide. In addition to reducing smokers’ desire for tobacco cigarettes [3, 4], warning labels have the potential to prevent initiation in non-smokers [5]. A systematic review of 20 countries reported that strengthening health warnings on cigarette packs was associated with increased knowledge of the harms of smoking, a reduction in smoking consumption, increased quit attempts and reduced smoking prevalence [2]. Novel, larger, graphic health warnings that convey a loss-framed message (focus on harms of smoking rather than gains from quitting) and lack of branding (standardised packaging), have been shown to increase attention to the message and improve perceptions of health risks and quitting-related behaviour [6–11].

E-cigarettes are a potential tobacco harm reduction product estimated to carry approximately 5% of the health risk of tobacco smoking [12–14]. Since their introduction, uptake and awareness has increased dramatically [15, 16]. An estimated 2.9 million adults in Great Britain currently use e-cigarettes [15, 16] over half (52%) of e-cigarette users are now former smokers and 45% are continuing smokers (dual users) [16]. Smoking cessation and reduction remain the most commonly cited reasons for use [16, 17]. Though some reports suggest otherwise [18], there is increasing evidence for their effectiveness for smoking cessation [19, 20].

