## Method

### Design

An experimental, randomised design will be used, with Smoking status (Smoker vs. Non-smoker), TPD presence (TPD1 vs. TPD2 vs. No-TPD; see below) and COMP presence (Presence vs. Absence) as between subjects independent variables, and Time (pre-post exposure of images/health messages) as a within subjects factor. Dependent variables comprise self-reported perceived harm, addictiveness, social acceptability, effectiveness, intentions to purchase and use of e-cigarettes. Smoking dependence, previous e-cigarette exposure, and baseline intentions to quit will be measured as covariates. For the E-cigarette Health Message factor, participants will be exposed to one of the six stimuli versions (see below). Messages will be displayed on e-cigarette packages as per the current EU-TPD warning labels on e-cigarette products. Warning label stimuli are:TPD1: TPD health warning as per currently implemented in the UK. “*This product contains nicotine which is a highly addictive substance*”TPD2: TPD longer health warning as currently implemented in many EU countries: “*This product contains nicotine which is a highly addictive substance. It is not recommended for non-smokers*”COMP: Comparative health message as generated in the pilot study (using the same parameters used for the TPD warning labels; font, font colour, size and placement on the pack)TPD1+: The TPD health warning (TPD1) in combination with the comparative message (using the same parameters above)TPD2+: The TPD longer health warning (TPD2) in combination with the comparative message (using the same parameters as above).No message: A no message condition using the same e-cigarette packages

The primary outcome variables for this study will be smokers’ and non-smokers’ perceptions of e-cigarettes associated with i) harm, ii) addictiveness, iii) social acceptability, iv) effectiveness, v) intentions to purchase, and vi) intentions to use e-cigarettes. Key outcome variables specifically for smokers will be intentions (i) to quit and (ii) use e-cigarettes in a quit attempt. All measures will be taken before and after exposure to messages.

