### Statistical analysis

Firstly, a series of ANCOVAs will be used to test for differences between TPD1 and TPD2 scores on Time 2 perceived ratings of e-cigarette i) harm, ii) addictiveness, iii) social acceptability, iv) effectiveness, v) intentions to purchase and vi) intention to use. We will control for Time 1 measurements of the dependent variable (DV) in each analysis (thus testing differences between TPD1 and TPD2 conditions, controlling for baseline differences).

If no differences between TPD1 and TPD2 are observed, we will collapse these two conditions. The subsequent analysis will use a series of ANCOVAs with 3 between-factors Smoking status (Smoker vs. non-smoker), TPD presence (Present vs. Absent), COMP presence (Present vs. Absent). Dependent variables (DV) will consist of Time 2 perceived ratings of e-cigarette i) harm, ii) addictiveness, iii) social acceptability, iv) effectiveness, v) intention to quit, vi) intention to purchase and vii) intention to use e-cigarettes. We will control for Time 1 measurements of the DV in each analysis (thus testing for change over time, controlling for baseline differences). All main and interactive simple effects will be tested, and we also specifically plan a-priori comparisons between the TPD/no COMP conditions against i) no TPD/no COMP, ii) TPD/COMP, iii) no TPD/COMP, and COMP alone with i) no TPD/no COMP, ii) TPD + COMP, iii) TPD/no COMP. These will be conducted at each level of smoking status.

In addition, the same ANCOVAs will be repeated with the same IVs, DVs and covariates, but additionally controlling for cigarette dependence, previous e-cigarette exposure, and baseline intentions to quit. If differences between TPD1 and TPD2 are observed, we will conduct the above analyses, with TPD presence being expanded to have 3 levels (TPD1 vs. TPD2 vs. No-TPD). The a-priori comparisons will be conducted twice as described above, once with TPD being replaced by TPD1 and the second time with TPD being replaced by TPD2.

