This area of research is important because smoking represents the greatest preventable cause of cancer. As reduced risk nicotine delivery products, e-cigarettes have the potential to decrease cancer prevalence if smokers are willing and able to switch. By putting such great emphasis on the potential addictiveness of e-cigarette products, TPD health warnings may deter smokers and dissuade e-cigarettes use in quit attempts. The influence of warning addictiveness labels on e-cigarettes have been demonstrated in previous studies which suggest that exposure to these warnings can both, increase harm perceptions and reduce intentions to use [35, 51]. In a between-subjects experiment, the addition of a warning label highlighting the addictiveness of e-cigarettes, led to an increase in risk perceptions and decrease in willingness to try the product whilst the same warning label on tobacco cigarettes did not have such an effect [36]; this suggests that the susceptibility vis-à-vis e-cigarettes’ abuse potential is greater than that of tobacco cigarettes. Given the public misperceptions of harm associated with e-cigarettes [16, 29], it is reasonable to posit that, the TPD health warnings are likely to further increase these misperceptions whilst decreasing intentions to purchase and use them in future quit attempts. Conversely, it has been previously shown that ‘lower risks’ warning labels on smokeless products have the ability to decrease harm perceptions [52]. Thus, in this study, we hypothesise that the addition of a comparative message (conveying the potential benefits of e-cigarette use to support cessation) will attenuate the effects of the TPD warnings in smokers. We do not have any a priori predictions regarding the effects of the comparative harm message in non-smokers. Ideally, a comparative harm message would reduce perceptions of harm in both smokers and non-smokers but increase intentions to use in smokers only.

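### In smokers, the only analysed e-cigarette use outcome cannot tell vaping alongside smoking from vaping to quit, and the quit-attempt use rating that could help is missing from the ANCOVA lists

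*Protocol article*

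**What the plan says.** **Items.** Table 1 (Outcome variables) gives all participants the general rating "How likely are you to use an e-cigarette", over one month and six months, on a 7-point scale. Smokers get two further items over the same horizons: "How likely is it that you will make a quit attempt" and "How likely are you to use an e-cigarette in a quit attempt". All are rated before and after exposure.

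**Status of the outcomes.** The Design section lists general intention to use among the primary outcomes, then adds: "Key outcome variables specifically for smokers will be intentions (i) to quit and (ii) use e-cigarettes in a quit attempt".

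**Aim for smokers.** The Objectives, repeated at the start of the Discussion, speak of smokers' purchase and use of e-cigarettes in their future attempts to quit.

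**Analysis.** Statistical analysis has two outcome lists. The preliminary comparison of TPD1 with TPD2 covers harm, addictiveness, social acceptability, effectiveness, purchase and general use. The main ANCOVA list covers the same four perceptions and ends "v) intention to quit, vi) intention to purchase and vii) intention to use e-cigarettes". The further-adjusted ANCOVAs reuse those outcomes. Use in a quit attempt is in neither list.

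**Population.** Inclusion/exclusion criteria exclude exclusive vapers and dual users.

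**Direction.** The abstract hopes to find messages that get smokers, but not non-smokers, to use e-cigarettes. The Discussion describes a rise in use intention confined to smokers as the ideal result and closes with a similar hope.

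**The concern.** The expected benefit to smokers comes from vaping in place of smoking. The abstract worries that warnings may "deter smokers from initiating use and substituting their tobacco smoking for e-cigarettes use if their content is deemed too negative", and the Discussion says "e-cigarettes have the potential to decrease cancer prevalence if smokers are willing and able to switch". Enrolled smokers do not currently vape. For them, starting to vape without giving up cigarettes is dual use, and the general rating does not distinguish this from vaping in order to stop.

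The error could run either way. A comparative message could be preferred because it raised intended vaping alongside smoking. A TPD warning could be reported as putting smokers off e-cigarettes as a route out of smoking when only intended additional use had fallen. The study is meant to inform policy on pack messages, so this reading matters.

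**Working it through.** No figure in the article bears on this point, so the check sets the sections side by side.

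**1. Which outcomes are planned, collected and analysed for smokers**

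| Outcome in smokers | Status in Design | Rated before and after (Table 1) | Named in Hypotheses | TPD1 v TPD2 list | Main ANCOVA list |
|---|---|---|---|---|---|
| General use | Primary | Yes | H2 | Yes | Yes |
| Quit intention | Key, smokers | Yes | H3 | No | Yes |
| Use in a quit attempt | Key, smokers | Yes | No | No | No |

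The outcome closest to the stated smoker objective is the only one of the three with no planned analysis.

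**2. What the general rating can distinguish.** Take the ends of the 7-point scale as an illustration.

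- Smoker A will vape but has no plan to stop smoking: general use 7, quit intention 1, use in a quit attempt 1.
- Smoker B will vape in order to stop: general use 7, quit intention 7, use in a quit attempt 7.

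The two are identical on general use and differ by 7 − 1 = 6 points on each of the other items.

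**3. Why separate ANCOVAs on use and quit intention do not settle it.** Take two smokers under each of two messages.

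- Message X: use ratings (7, 1), quit ratings (1, 7). Mean use = (7 + 1)/2 = 4; mean quit = (1 + 7)/2 = 4. High use with low quit intention: 1 of 2.
- Message Y: use ratings (7, 1), quit ratings (7, 1). Mean use = 4; mean quit = 4. High use with low quit intention: 0 of 2.

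The means agree, but the number intending to vape without quitting does not. Only the joint distribution, or an item that links use to quitting, shows the difference.

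**4. Could the ANCOVA lists already cover it?** Outcome variables treats general use as its own outcome and puts quitting and quit-attempt use together under a single later number. One might therefore read the listed quit intention as shorthand for both. But Design numbers them as two outcomes and Table 1 gives them separate questions, so the lists as written do not include the second.

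**The case against.** The strongest reply is that much of the safeguard is already there. Quit intention is a key smoker outcome, is the subject of H3 and is in the main ANCOVA list. A message that only added vaping would tend to raise use and leave quit intention flat, and the collected data could show this. The general item also has a proper purpose: smokers and non-smokers must be compared on a common outcome, and non-smokers cannot be asked about quitting. The abstract's worry covers initiating use as well as substituting, and general use measures the former directly.

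All of this stands, and it is why general use should be kept. It does not explain why a key smoker outcome that matches the Objectives has no planned analysis. Nor does the article say how a rise in use with no change in quit intention would be read.

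A reader might go further and infer that substitution is the stated aim and that the plan counts dual use as success. The documents do not support that. Substitution and switching appear as rationale; the objective is worded as use in quit attempts and the hope as use among smokers. No success rule is defined, so the favourable direction is inferred from the abstract and Discussion.

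**Conclusion.** The point holds as a mismatch between the smoker objective and key outcome on one side and the analysed outcomes on the other, made worse by a use item that is ambiguous for smokers. It should be corrected, but the data remain usable because the needed ratings are already planned.

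No numerical size can be given. A reader might take the Background figures on existing users (52% former smokers; "45% are continuing smokers (dual users") to mean that close to half of any rise in smokers' use intention would be intended dual use. Those figures describe people already vaping at one time. They say nothing about how intentions prompted by a message would divide, and a share of users does not translate into a share of a change on a 7-point rating.

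The conclusion assumes that the outcome lists mean what they say and that the smoker result will be read in the direction the abstract and Discussion indicate. It does not require dual use to be harmful, only that it differs from vaping to stop smoking. The quit-attempt rating narrows the gap but does not close it, since intending to use an e-cigarette in an attempt is not the same as switching completely.

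**What to change.** In Statistical analysis:

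1. Add use of an e-cigarette in a quit attempt to both outcome lists as a smoker-only ANCOVA outcome at Time 2, adjusted for its Time 1 value, with TPD presence and COMP presence as factors and the same a-priori comparisons.
2. State that the conclusion about encouraging use among smokers rests on this outcome together with quit intention. Keep general use for comparing smokers with non-smokers.
3. As a supporting analysis, show by arm the joint distribution of smokers' Time 2 general use and quit intentions, with cut-points and time horizon fixed in advance, so that use without quitting is visible.
4. State that a rise in general use alone will not be read as substitution.

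No new data are needed. The main list goes from 7 to 8 outcomes, a small addition to multiplicity, and cutting two 7-point ratings loses some information, so step 3 should stay supporting. A new item on switching completely is optional. It would echo one of the candidate comparative messages and, asked before exposure, could prime the other arms or hint at the aim, which the Discussion wants to avoid.

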### Study setting/procedure

Participants will be contacted by the panel agency and provided with a link. On clicking the link they will be presented with an online information sheet and then prompted to provide consent. Participants will be asked to rate the images on the constructs highlighted in Table 1 (i.e. all items measuring perceptions and intentions) before and after presentation of the allocated health message displayed on a series of different e-cigarette images. Thereafter, they will be presented with the non-related filler questions, before completing a set of questionnaires to collect demographic information such as age, gender, ethnicity, occupation, SES, highest qualification, smoking status and past e-cigarette use. The FTCD [50] and MTSS questionnaires [49] will be administered to smokers only, to measure cigarette dependence and motivation. Lastly, participants will be presented with an on-screen debriefing information letter.

### Data management and planned dissemination

The study will use a panel agency that is GDPR (General Data Protection Regulations) compliant. All data will be kept in accordance with the study protocol and with GDPR’s requirements under password protected networked PCs and any documents on hard copies in locked filing cabinets in a locked office. Once finalised, anonymised data will be deposited on the University’s open data repository. The data collected are intended to benefit the general public and to inform policy decision making; we will therefore preserve all data resulting from the study (with the exception of personal data) and make it publically available with as few restrictions as possible. The data will be given a CC-BY license which will require any future users to acknowledge the investigators in any subsequent publications arising from use of the data. We will disseminate a lay summary, explaining our findings and their importance. The findings will be disseminated via open access peer-review publication, conference presentations and press releases, and shared with a number of charities, practitioners and public health and policy organisations via presentations, briefing papers and web-based material.

